### Additional consent provisions for collection and use of participant data and biological specimens {26b}

Since the study protocol does not include the collection of any extra participant data or biological samples, additional consent procedures are not required.

## Assignment of interventions: allocation

### Sequence generation {16a}

A covariate-adaptive randomization (minimization) approach with a random element will be employed to allocate participants in a 1:1 ratio to the intervention arms. This method is specifically designed to maintain balance across key prognostic variables in trials with moderate sample sizes and multiple baseline covariates, while preserving allocation unpredictability [64, 65]. Randomization will be implemented centrally using a pre-specified Python-based algorithm, executed by an independent research assistant following completion of baseline assessments. The algorithm evaluates imbalance across predefined covariates—including study site, gender, baseline depression severity, and psychiatric comorbidity—and assigns participants to the treatment arm that minimizes overall imbalance, with a probabilistic element (i.e., less than 100% deterministic assignment) to reduce predictability. This approach avoids the limitations of excessive stratification and fixed block randomization while ensuring transparent, reproducible, and auditable allocation. A detailed description of the randomization algorithm, operational procedures, and audit trail is provided in Supplementary File A, and Fig. 3 presents the CONSORT flow diagram illustrating participant allocation.

**Fig. 3 Fig3:**
[figure not shown]
CONSORT flow chart of randomization

### Concealment mechanism {16b}

An independent research assistant will generate the randomization sequence using covariate-adaptive algorithms accounting for age, gender, depression severity, and comorbidity, with a 1:1 allocation to treatment groups. The randomization sequence will be securely stored in password-protected documents accessible exclusively to the principal investigator and the designated research assistant, with access logs maintained for auditing purposes. Allocation concealment will be ensured until assignment, and outcome assessors and data analysts will remain blind to group allocation throughout the trial. Due to the nature of the intervention, blinding of clients to treatment delivery mode (online vs. in-person EMDR) is not feasible. Group assignment will be implemented electronically via either OpenClinica (https://www.openclinica.com) or Sealed Envelope (https://www.sealedenvelope.com) platforms, which reveal only the immediate next assignment following completion of baseline assessments. This dual protection system—combining restricted access to master randomization lists with electronic allocation masking—ensures compliance with CONSORT and SPIRIT standards for allocation concealment.

### Implementation {16c}

Following eligibility confirmation and baseline assessments (T_1_), randomization will be executed through the designated electronic platform (OpenClinica/Sealed Envelope) by a research assistant who will not be involved in outcome measurement. The online system will be connected to the therapists’ and patients’ emails. It will automatically notify the treating therapist of the allocated intervention mode (online or in-person) and inform the patient via secure messaging, while maintaining the blinding of outcome assessors. To ensure protocol fidelity, therapists will receive arm-specific procedure checklists corresponding to their notification. The principal investigator will conduct weekly cross-checks between the electronic allocation records and physical randomization documents to detect and rectify any discrepancies.

## Assignment of interventions: blinding

### Who will be blinded {17a}

Due to the single blind-nature of intervention, complete blinding is not feasible for clients or therapists regarding delivery mode (online vs. in-person EMDR). However, therapists will remain blind until after completing the initial consultation with clients. Outcome assessors (research assistants) and data analysts will maintain full blinding throughout the trial. To minimize bias:Outcome assessors will perform clinical evaluations before therapy sessions begin and without access to subsequent treatment setting information.Data analysts will work with de-identified datasets using group codes.For fidelity analysis, independent reviewers will assess edited audio/video recordings with all platform-specific references removed.Blinding success will be empirically evaluated at the study midpoint by asking blinded personnel to guess group allocations, with ≤ 60% correct guesses indicating adequate maintenance of blinding.

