### Procedure for unblinding if needed {17b}

Unblinding will be permitted only in exceptional circumstances (e.g., severe destabilization, emotional dysregulation, or psychiatric deterioration) or if critical data errors emerge during post-assessment analysis. The process will be initiated either by the treating therapist (for clinical emergencies), or the research assistant handling data (for analytical issues) via a secure email request to the principal investigator. Upon receipt, the principal investigator will:Verify the necessity through documented clinical justification or data error reports.Disclose only the minimally required treatment allocation or data details to the requesting party.Record the unblinding event with timestamp, rationale, and disclosed information in the trial’s master log.

Notably, patients will not be informed of their group allocation unless medically imperative (e.g., for subsequent emergency care). All unblinding events will be reported to the ethics committee as protocol deviations.

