## Data collection and management

### Plans for assessment and collection of outcomes {18a}

Primary outcomes (depression severity assessed) and secondary outcomes (anxiety symptoms measured) will be collected at four timepoints: baseline (T1), mid-therapy (T2), post-intervention (T3), and 2-month follow-up (T4). All clinical ratings will be administered by trained research assistants who are blinded to treatment allocation. The feasibility and acceptability of the online platform will be evaluated using three validated instruments, as outlined in the protocol. Treatment fidelity and therapist competence will be assessed through both qualitative and quantitative methods, also detailed in the protocol. Data integrity will be ensured through automated checks for missing values and outliers, complemented by audits conducted by the statistical analyst. Any discrepancies will prompt source document verification by an independent monitor or research assistant.

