### Plans to promote participant retention and complete follow-up {18b}

To maximize participant retention and follow-up completion, a multipronged strategy will be employed, including:Regular check-in calls to address logistical or technical barriers.Flexible scheduling options, including evening and weekend sessions to accommodate working participants.A three-tiered follow-up procedure for missed appointments:Day 1: Email reminder.Day 3: Follow-up mobile/telephone call by a research assistant.Dedicated “therapy booster” sessions for patients showing signs of disengagement (defined as ≥ 2 missed appointments).Monthly retention reports, reviewed by the principal investigator to identify trends and adjust engagement strategies as necessary.

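### The only assessor-blinding measure the article describes cannot reach the T3 HAM-D-17 rating, rater and caller roles are not separated, and the 60% guess rule cannot show that the blind held

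*Protocol article*

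**What the plan says.** All places are in the protocol article.

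- **Blinding is asserted at every rating.** Who will be blinded {17a}: "Outcome assessors (research assistants) and data analysts will maintain full blinding throughout the trial". Plans for assessment and collection of outcomes {18a}: "All clinical ratings will be administered by trained research assistants who are blinded to treatment allocation". The same section lists ratings at T1, T2, T3 and T4 (two-month follow-up). Concealment mechanism {16b} also says that assessors and analysts stay blind.
- **The measure described for assessors.** {17a}: "Outcome assessors will perform clinical evaluations before therapy sessions begin and without access to subsequent treatment setting information".
- **The primary endpoint.** Outcomes {12} defines it as the HAM-D-17 change from T01 to T03.
- **Clients know their arm.** {16b} and {17a} say that clients cannot be blinded to delivery mode. In Implementation {16c} the system will "inform the patient via secure messaging, while maintaining the blinding of outcome assessors".
- **A conflicting statement.** Procedure for unblinding {17b}: "Notably, patients will not be informed of their group allocation unless medically imperative".
- **Who telephones clients.** Plans to promote participant retention {18b} lists, for day 3 after a missed appointment: "Follow-up mobile/telephone call by a research assistant". It also lists check-in calls about logistical or technical barriers, without naming the caller.
- **Role separation.** {16c} keeps the assistant who runs the randomisation out of outcome measurement. No similar separation is stated for other assistants.
- **The blinding check.** {17a} sets one check at the study midpoint, by "asking blinded personnel to guess group allocations, with ≤ 60% correct guesses indicating adequate maintenance of blinding".

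**The concern.** The HAM-D-17 is scored by a rater who talks to a client who knows whether treatment was online or in person. The primary comparison is online minus in-person change, judged against a 3-point non-inferiority margin (Statistical methods {20a}). A rater who learns the arm and expects one mode to do better or worse can move that difference in either direction. Rater blinding is the main protection, so three things matter: whether the stated measure works at T3, whether raters have other contact that could reveal the mode, and whether the stated check could detect a failure.

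On the article's wording, the measure stops at the start of therapy, the contact is not ruled out, and the check is too blunt to certify the blind. In addition, {17b} treats the client as someone from whom allocation is withheld, although the client is the most likely source of a leak to the rater.

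**Working it through.** **1. Does the stated measure reach T3?**

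| Rating | Before therapy starts? | Setting information still in the future? |
|---|---|---|
| T1, baseline | yes | yes |
| T2, mid-therapy | no | no |
| T3, end of treatment (primary) | no | no |
| T4, two-month follow-up | no | no |

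Read literally, the measure covers T1 only. If it means before a given day's session, it could cover T2, but hardly T3 or T4, when treatment is over. On neither reading does it explain how the T3 rater stays blind.

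**2. Can a rater also be a caller?** Raters are research assistants ({17a}, {18a}). The day-3 caller is a research assistant ({18b}). The only stated bar on combining roles concerns the randomising assistant ({16c}). Overlap is therefore not stated, but it is not excluded.

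**3. What does 60% correct mean?** The article gives no derivation for the cut-off, so there is no figure of its own to reproduce. Inputs: 1:1 allocation (Sequence generation {16a}), so a pure guess is right half the time; cut-off 0.60 ({17a}). Let q be the share of clients whose arm the rater knows.

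Expected correct share = q + (1 − q) × 0.5

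Setting this to 0.60 gives q = (0.60 − 0.50) / 0.50 = 0.20.

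The result depends on how raters guess the remaining clients. With guess accuracy g, q = (0.60 − g) / (1 − g): 33% at g = 0.40, 27% at 0.45, 20% at 0.50 and 11% at 0.55.

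**4. How often does the rule pass?** The number of guesses is not stated. Forty is an assumption, taken from the midway point used for the fidelity review (Strategies to improve adherence {11c}); 80 is shown for comparison. The rule passes with at most 24 of 40, or 48 of 80, correct. P(pass) is the exact binomial probability at p = 0.5 + 0.5q.

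| Share known, q | True correct rate, p | P(pass), 40 guesses | P(pass), 80 guesses |
|---|---|---|---|
| 0 | 0.50 | 0.92 | 0.97 |
| 0.20 | 0.60 | 0.56 | 0.54 |
| 0.30 | 0.65 | 0.31 | 0.20 |
| 0.40 | 0.70 | 0.12 | 0.04 |

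**5. What does a pass at the limit show?** An observed 24/40 has an exact 95% CI of 43% to 75%. With coin-flip guessing on the rest, the upper limit corresponds to q = 2 × 0.75 − 1 = 0.50. Such a pass is compatible with no unblinding and with half the clients being known.

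**6. When is the check made?** If the midpoint is 40 completed therapies, about 40 of the 80 planned T3 ratings exist by then. The check says nothing about the other half.

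**7. Do the statements on client knowledge agree?** {16b} and {17a} say that clients cannot be blinded, and {16c} has the system message the allocation to them. {17b} says that they are not informed except in medical need. Both cannot stand.

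**The case against.** The strongest reply is that the article says three times that assessors are blind ({16b}, {17a}, {18a}), and that {16c} sends the allocation to therapist and patient only. A condensed article need not print rating scripts, rating locations or instructions to clients. This stands against any claim that the T3 rating is unprotected. A reader might infer that; the document supports only that no measure described there secures blinding at T3. The reply does not rescue the printed measure, because its wording confines it to the time before therapy.

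A second reply is that several assistants exist, that Data management {19} limits each to forms relevant to their duties, and that a missed-appointment call need not reveal the arm. This also stands in part. A reader might conclude that raters do make the calls, or that they meet clients at the clinic or on the therapy platform. The article says neither. But limits on form access are not a bar on telephoning clients, and calls about technical barriers could well disclose the mode.

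A third reply is that at q = 0.20 the rule passes only slightly more often than it fails. That is correct, and it is wrong to say that the rule reliably passes such a blind. It is equally wrong to treat a pass as evidence of adequate blinding.

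Finally, one might put the possible bias in HAM-D-17 points or as a share of the 3-point margin. That needs an assumed rating shift for which the document gives no basis, so no such figure is offered.

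**Conclusion.** The point holds in limited form. Blinded rating is asserted throughout, but the assessor measure described cannot deliver it at T3. Separation of raters from callers is incomplete as written. {17b} contradicts {16b}, {16c} and {17a}.

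The ≤ 60% rule is a weak threshold: its limit is the expected result when one client in five is known to the rater, and it then passes with probability 0.56 (40 guesses) or 0.54 (80 guesses). At 30% known it still passes with probability 0.31 or 0.20. These figures rest on coin-flip guessing for the remaining clients, independent guesses, and an assumed number of guesses. The finding on the measure's timing and the contradiction rest on the text alone. The direction and size of any effect on the primary difference cannot be determined from the document. The changes are worth making because they are cheap and bear on the primary endpoint.

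**What to change.** 1. Reword {17a} so that the safeguard covers T2, T3 and T4. State that ratings are held apart from therapy sessions and the therapy platform, and that each rating opens by asking the client not to disclose the delivery mode.
2. In {18b}, bar assistants who rate outcomes from retention, check-in and technical calls, dividing these tasks among the existing assistants.
3. At each remaining T3 rating, record the rater's guess of the arm and the reason for it. Replace the midpoint ≤ 60% rule with results by arm and 95% CIs. Add a sensitivity analysis of the primary comparison that excludes ratings where the rater reported learning the arm.
4. Reconcile {17b} with {16b}, {16c} and {17a} by removing the statement that patients are not informed of their allocation.

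Cost: wording changes, one extra form item, some reallocation of tasks and one extra analysis. Sample size and treatment are unaffected. According to Trial status, recruitment began in April 2025 and was expected to finish by the end of February 2026. The rating channel should therefore not be switched for clients already rated at T1, since that would put the two halves of their change score on different channels. Guesses for T3 ratings already made cannot be recovered reliably, so the report should say how many ratings the new record covers.

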### Procedure for unblinding if needed {17b}

Unblinding will be permitted only in exceptional circumstances (e.g., severe destabilization, emotional dysregulation, or psychiatric deterioration) or if critical data errors emerge during post-assessment analysis. The process will be initiated either by the treating therapist (for clinical emergencies), or the research assistant handling data (for analytical issues) via a secure email request to the principal investigator. Upon receipt, the principal investigator will:Verify the necessity through documented clinical justification or data error reports.Disclose only the minimally required treatment allocation or data details to the requesting party.Record the unblinding event with timestamp, rationale, and disclosed information in the trial’s master log.

Notably, patients will not be informed of their group allocation unless medically imperative (e.g., for subsequent emergency care). All unblinding events will be reported to the ethics committee as protocol deviations.

## Interventions

### Explanation for the choice of comparators {6b}

The comparator is the in-person delivered EMDR therapy and is selected as the active control because it represents the current evidence-based standard of care for the treatment of depressive disorder [66]. Online EMDR therapy is an experimental intervention under investigation for non-inferiority. This design allows determining whether the novel online delivery method preserves therapeutic efficacy while offering potential accessibility benefits.

### Intervention description {11a}

This trial employs the evidence-based DeprEnd EMDR therapy protocol for depressive disorders [67]. This protocol is specifically optimized for depressive disorders through modifications in:History-taking (focused on depressive triggers vs. trauma),Preparation (enhanced psychoeducation on depression maintenance), andInstallation (targeting depressive cognition reprocessing) [21].

The DeprEnd EMDR therapy protocol has been culturally and methodologically adapted for the Pakistani context, and the full adaptation process has been published elsewhere [42]. In the present trial, both study arms follow the same adapted protocol, differing only in mode of delivery. The intervention will be delivered over 10–14 weekly sessions, depending on individual clinical presentation and treatment response. Each session will last approximately 60–90 min, consistent with standard EMDR therapy practice.In-person EMDR therapy will be delivered by EMDR-certified therapists in selected psychotherapy clinics. Sessions will follow the adapted DeprEnd EMDR protocol using standard face-to-face procedures, including therapist-guided bilateral stimulation and adherence to protocol fidelity requirements.Online EMDR therapy will be delivered via the BilateralBase platform, a validated telehealth system developed in the UK [68]. Therapists and clients will connect synchronously via secure video conferencing using a computer or mobile device. The platform provides visual and auditory bilateral stimulation, real-time therapist guidance, and session structuring consistent with in-person EMDR delivery. Session recordings are enabled for fidelity monitoring, with appropriate consent and ethical safeguards. Apart from delivery modality, the content, session structure, and therapeutic procedures remain equivalent to those used in the in-person arm.

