### Outcomes {12}

#### Primary outcome

The primary outcome of the study is to study the change in depressive symptom severity. It will be assessed by using the Hamilton Depression Rating Scale-17 [69]. Depression assessments will be conducted at baseline (T01), mid-treatment (T02), end-of-treatment (T03), and follow-up (T04). The primary endpoint for evaluating clinical effectiveness and non-inferiority is the change in depression scores from baseline (T01) to end-of-treatment (T03).

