### Participant timeline {13}

The participant timeline is presented in Fig. 4 on the next page. Patient enrollment will occur at the T_1_ timepoint, which will also include the informed consent process, initial diagnostic interviews, and baseline symptom assessments. Following enrollment, patients will be allocated to either online EMDR or in-person EMDR therapy, with this group assignment maintained throughout the study duration. Regarding assessments:Demographic characteristics and baseline clinical features will be collected at therapy initiation (T_1_).Primary outcome measures (depression and comorbid anxiety symptoms) will be assessed at four key timepoints: baseline (T_1_), mid-therapy (T_2_), therapy completion (T_3_), and follow-up (T_4_) to evaluate temporal patterns of symptom reduction.Treatment fidelity evaluations will be conducted at the mid-therapy point (T_2_) through standardized protocol adherence checks.

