## Statistical methods

### Statistical methods for primary and secondary outcomes {20a}

All quantitative analyses in Phase two and Phase three will be conducted using appropriate statistical methods aligned with the study design, outcome structure, and hypotheses. Analyses will be performed using standard statistical software (e.g., SPSS and Python 3.10+, standard statistical libraries). Phase two analyses will focus on feasibility, acceptability, safety, and preliminary symptoms change following delivery of the culturally adapted DeprEnd EMDR protocol. Feasibility indicators will be summarized using descriptive statistics, and a one-sample t-test with 95% confidence intervals and significance levels. Repeated-measures General Linear Models will be used to determine temporal symptoms changes. These analyses will be exploratory and will not be intended to establish definitive clinical effectiveness.

Phase three analyses will be conducted within a randomized controlled trial framework. First, non-inferiority is evaluated by comparing the estimated 95% confidence interval for the between-group difference to a pre-specified margin; if the upper bound lies entirely below the margin, non-inferiority is concluded [81]. For the primary outcome, non-inferiority is based on the between-group difference in change scores on the Hamilton Depression Rating Scale-17 from baseline (T1) to the end of treatment (T3), calculated as online EMDR minus in-person EMDR. A non-inferiority margin (δ) of 3 points was pre-specified a priori, consistent with previously published non-inferiority trials that defined margins on this scale [82]. For secondary outcomes of anxiety, as assessed by the Generalized Anxiety Disorder-7, between-group differences in change scores will be examined using analogous comparative principles and reported with effect estimates and confidence intervals. A non-inferiority margin (δ) of approximately 2.5 points on this scale was pre-specified a priori, informed by clinically meaningful score differences used in prior non-inferiority psychotherapy trials [83].

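### The primary rating falls at therapy completion and course length varies with response, so timing and dose can differ by arm in a direction that favours non-inferiority

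*Protocol article*

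**What the plan says.** **Course length.** Intervention description {11a}, for both arms: "The intervention will be delivered over 10–14 weekly sessions, depending on individual clinical presentation and treatment response". The section states no objective rule for ending or extending a course and names no one who decides.

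**Primary endpoint.** Outcomes {12}: "The primary endpoint for evaluating clinical effectiveness and non-inferiority is the change in depression scores from baseline (T01) to end-of-treatment (T03"). Participant timeline {13} calls the same visit therapy completion, and Plans for assessment {18a} calls it post-intervention. The text shown attaches no week to it.

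**Who knows the arm.** Under Implementation {16c} the allocation system informs the treating therapist of the delivery mode. Under Who will be blinded {17a}, "complete blinding is not feasible for clients or therapists regarding delivery mode". For the ratings, the same section says: "Outcome assessors (research assistants) and data analysts will maintain full blinding throughout the trial".

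**Decision rule.** Statistical methods {20a}: "A non-inferiority margin (δ) of 3 points was pre-specified a priori". It is applied to the difference in change scores, online minus in-person, through the upper limit of a 95% confidence interval. The section describes no account of sessions received or time to T3 in this comparison. Session count serves as the time axis of the secondary hierarchical model, and attendance enters an exploratory dose–response analysis in {20b}.

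**The concern.** A client who responds quickly may finish near session 10 and be rated then. A client who responds slowly may continue to session 14 and be rated about four weeks later, after more therapy and more time for natural recovery. If online delivery is slower, more online clients fall in the second group. The response-driven length then offsets part of the very difference that the trial is meant to detect.

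In a superiority trial this would count against the claim. Here it counts in favour, because anything that brings the arms together moves the upper confidence limit below the margin. No therapist need act in a biased way: an even-handed practice of treating until response is enough. Knowledge of the arm opens a second route. Blinded assessors protect the score itself, but neither the date of the rating nor the number of sessions before it.

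At stake is what a positive result would mean. Explanation for the choice of comparators {6b} asks whether online delivery preserves efficacy, and {11a} presents mode of delivery as the only difference between arms. With response-driven length, dose and observation time may differ as well.

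**Working it through.** The plan gives no figure for this effect, so there is none to reproduce. The steps show what the plan's own numbers imply and what has to be assumed.

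**Inputs from the article:** 10 to 14 weekly sessions ({11a}); margin 3 points ({20a}); SD of change 8 and 40 per arm ({14}). The plan's sample-size formula gives 7.84 × 128 / 25 = 40.14, which agrees with its 40.

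**Not in the article:** improvement per session, any difference in speed between the arms, and the rule for ending a course.

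**Step 1. Precision.** SE = 8 × √(2/40) = 1.789. The 95% half-width is 1.96 × 1.789 = 3.51. Non-inferiority therefore needs an observed difference below 3 − 3.51 = −0.51, that is, online about half a point better. The chance of declaring it at a true T3 difference d is Φ((3 − d)/1.789 − 1.96):

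| True difference at T3 | Chance of declaring non-inferiority |
|---|---|
| 3.0 | 2.5% |
| 2.5 | 4.6% |
| 2.0 | 8.1% |
| 1.5 | 13.1% |

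**Step 2. Ceiling.** The masking cannot exceed 4 sessions × improvement per session. The documents do not give the second factor.

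**Step 3. Illustration (all assumed).** Mean baseline 24; linear improvement of 1.0–1.6 points per session in person; between-client SD of that rate 0.3 or 0.55; online rate 70–80% of in-person. The course ends at the first session from 10 to 14 at which a 50% or 60% reduction is reached. The 60% figure is borrowed from the article's responder definition ({30}), which is not a stopping rule. At 1.4 points per session, online at 75% and a 60% threshold, the online-minus-in-person differences are:

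| | SD of rate 0.3 | SD of rate 0.55 |
|---|---|---|
| Every client given 12 sessions | 4.1 | 3.8 |
| Response-driven length, rated at completion | 2.4 | 2.9 |
| Response-driven length, rated at week 14, scores flat after therapy | 2.4 | 2.9 |
| Mean sessions, in-person / online | 11.42 / 12.92 | 11.65 / 12.58 |

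Over all the assumed settings, online clients received 0.4 to 1.9 more sessions, and the T3 difference was 0.3 to 2.4 points smaller than with 12 sessions for everyone.

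**Step 4. Effect on the decision.** Putting these values into the Step 1 formula, the chance of declaring non-inferiority rises from 0.5% (d = 4.1) to 5.2% (d = 2.4), or from 0.8% (3.8) to 2.8% (2.9).

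**Step 5. What a fixed visit recovers.** Rows two and three of the table are equal: the shrinkage comes from dose, not from the date of the rating. A week-14 visit adds back only recovery after therapy ends. If that is 0.2–0.4 points per week (assumed), the arms differ by 12.92 − 11.42 = 1.50 weeks or 12.58 − 11.65 = 0.93 weeks. That gives at most 0.30–0.60 or 0.19–0.37 points.

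**The case against.** **Flexible length is a legitimate target.** Both arms follow the same flexible protocol, and the Discussion describes a hybrid effectiveness–implementation view. Outcome at the end of a course as actually delivered is a fair question. This stands, but a result on that question says little about preserved efficacy unless sessions used are compared by arm, and the article states no such comparison.

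**The mechanism is partly inferred.** The article does not say that the therapist sets the length, or that poor response leads to more sessions. It also names clinical presentation as a driver, and minimisation on site, gender, severity and comorbidity should roughly balance that between arms. This stands too. Response is nevertheless named as a driver, and the treating therapist is the natural reading.

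**A reader might infer a bias of 2 to 4 points**, from four weeks at 0.5–1.0 points per week, enough to absorb the margin. The documents do not support this. The slope is assumed, every online client would need 14 sessions and every in-person client 10, and clients kept on for poor response probably improve more slowly than average.

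**A reader might infer that a fixed-week rating cures the problem.** Step 5 shows that it does not: with course lengths unchanged it equalises observation time only.

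**A reader might also object that the mid-therapy visit (T2) cannot be placed** while the total number of sessions is unknown. That is visit-window detail which an article may leave to the full protocol.

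**The timeline figure is not shown** and may carry weeks. If it does, the text defining T3 by therapy completion would need to be reconciled with it.

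**Conclusion.** The point holds in limited form. The deciding rating is tied to therapy completion, completion varies with response, and therapists know the arm. Timing and dose before the primary rating can therefore differ by arm, in the direction that favours the trial's claim.

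The size is not derivable from the documents. It is bounded by four sessions and requires online delivery to be slower in the first place. Under the assumptions in Step 3 it is 0.3 to 2.4 points. In the worked examples it raises the chance of wrongly declaring non-inferiority to no more than about 5%, because the planned precision already makes that declaration hard to reach. The examples also shrink less when clients vary more in their rate of improvement.

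This is a worthwhile and inexpensive improvement to the endpoint definition and the reporting. It does not invalidate the design.

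**What to change.** Leave the session range and all decisions on ending therapy as they are.

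1. **Fix the primary rating in time.** Take the primary HAM-D-17 rating at one set time after randomisation in both arms, no earlier than the end of the longest planned course (for example week 14, with a stated window), whatever number of sessions was used. Record any post-trial booster session ({30}, {34}) received before it: a client who finishes at week 10 could have one by week 14. State whether the two-month follow-up counts from this visit.
2. **Report dose and duration by arm.** Pre-specify a comparison of sessions delivered and weeks to completion, shown beside the primary result. If the arms differ in dose, limit the conclusion to non-inferiority of the flexible-length course.

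Trial status says that recruitment began in April 2025. For clients already rated at completion, the rating date cannot be changed. Report their time to T3 and sessions by arm, and pre-specify a sensitivity analysis before allocation is revealed to the analysts.

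**Cost.** Protocol wording, visit windows and one added table; no extra visits for clients not yet rated. Early completers would be rated up to about four weeks after their last session. Some clients with pauses ({11b}) or rescheduled sessions ({11c}) might still be in therapy at the rating. Item 1 equalises observation time but not dose, so item 2 is needed with it.
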